### Theoretical framework of the self-management programme

Bandura’s construct of self-efficacy [16] will be adopted to guide the proposed programme design and implementation. Self-efficacy refers to an individual’s confidence to perform an action to reach a desired goal [16]. Judgment of one’s self-efficacy determines the course of action required, degree of effort, and perseverance to continue an action even in face of obstacles. Self-efficacy is developed through four sources of information namely mastery experience, vicarious experience, verbal persuasion, and minimising physiological or emotional arousal [16]. Substantial literature reported increased self-efficacy leads to modification of health behaviours, and better patient outcomes such as quality of life or perceived health status [9, 11]. Outcome expectation, another central construct of Bandura’s social cognitive theory, refers to an individual’s judgement of the likelihood that performance of a particular action will produce a certain outcome. It takes three major forms including physical, social and self-evaluative effects. Within each form, positive expectations serve as incentives while negative expectations serve as disincentives to one’s performance of an activity [16]. Bandura suggests that the initiation and continuation of a particular activity or behaviour would be best predicted by the combined influence of self-efficacy beliefs and types of outcome expectation. The stronger one believes in own ability to perform a specific activity and the outcome of that activity, the more likely that one will initiate and maintain the behaviour [16, 17]. In this study, the influences of self-efficacy and outcome expectancy beliefs on stroke survivors’ performance in stroke self-management behaviours will be addressed when designing the programme. Figure 2 outlines the theoretical framework of the programme. Table 2 summarises the strategies adopted to enhance participants’ self-efficacy and outcome expectation of performing self-management behaviours.

**Fig. 2 Fig2:**
[figure not shown]
Theoretical framework of the stroke self-management programme. (Adapted from Bandura [16])

**Table 2 Tab2:** Strategies adopted to enhance participants’ self-efficacy and outcome expectation of performing self-management behaviours

Sources of information of self-efficacy	Strategies adopted	Programme components
Mastery experience	- Establish a short-term goal and a realistic action plan. - Assist to break down difficult tasks into simple steps. - Practice the use of core self-management skills. - Revise the action plan if necessary. - Encourage to record the implementation of the action plan.	HV HV, GS GS GS, PF HV, GS, PF
Vicarious experience	- Guide the viewing of videos about experience sharing. - Facilitate experience sharing among the group.	HV, GS GS
Verbal persuasion	- Acknowledge incremental successes. - Provide positive reinforcement. - Reinforce the importance of ‘taking an active role’.	HV, GS, PF HV, GS, PF HV, GS, PF
Physiological & emotional arousal	- Assist to reinterpret negative physiological and emotional states.	HV, GS, PF
Outcome expectation	- Assess and reinforce the positive outcomes valued by the participants after performing stroke self-management behaviours.	HV, GS, PF

*GS* Group sessions, *HV* Home visit, *PF* Follow-up phone calls

### Programme contents

The nurse will schedule with the participants for home visit. During home visit, the nurse will assess the participant’s current medical, emotional and role management of their post-stroke conditions [4, 8], and their self-efficacy and outcome expectancy beliefs of performing self-management behaviours. Based on the assessment, the nurse will work with the participant to establish a short-term goal of importance to stroke recovery, and develop a realistic action plan to achieve the goal [4]. Information about stroke self-management and core self-management skills such as problem-solving and decision-making will be provided. Furthermore participants will be guided to view one to two video clips on the DVDs to enable them to learn from other stroke survivors’ experiences. Positive reinforcement will be provided to promote their confidence in implementing their action plans [16]. Participants will be encouraged to view the videos, read the programme booklet, and record the implementation of their action plans after the home visit.

In the following week after the home visit, two group sessions will be held on the same day in a community centre. During the group sessions, participants will be provided with information about the physical and psychosocial consequences of stroke, and practical tips for effective stroke self-management. More importantly, the nurse will act as a facilitator to encourage participants to reflect and share their barriers to and facilitators of implementing their action plans. Based on the common problems among the group, video clips of sharing by stroke survivors will be presented. Participants will be facilitated to explore own ways to address their barriers. Examples will be provided to guide their practice of core self-management skills to better implement their plans. If necessary, their action plans will be revised. Positive reinforcement will be provided and participants are encouraged to visualise their expected positive outcomes after performing the self-management behaviours [16]. Participants will be encouraged to continue implement their action plans and record their progress after the sessions.

Three weekly follow-up phone calls by the nurse will be provided after the group sessions to review the participant’s progress, barriers to and facilitators of implementing the action plans. Individualised feedback and positive reinforcement will be provided. Participants’ expected positive outcomes of achieving the goals will be reinforced. At the end of the last follow-up phone call, participants’ extent of goal attainment will be evaluated. They will be guided to continue, revise, or establish a new short-term goal for the next month.

### Control group: usual care

Participants in the control group will receive usual care provided to stroke survivors discharged to their home without any additional interventions. Usual care includes some or all of the following services: hospital- or community-based health education for example talks or leaflets; follow-up appointments in an outpatient clinic or a day hospital; medical consultations with a local general practitioner; referral to or information about local community-based services for people with stroke or disability for example meals on wheels.

### Outcome measures

#### Primary outcomes

##### Self-efficacy

The 13-item Stroke Self-Efficacy Questionnaire (SSEQ) will be used to measure participants’ self-efficacy in performing daily functional activities and self-management such as getting in or out of bed, preparing meals, or persevering to make progress [18]. Each item is rated on an 11-point Likert scale (0 = ‘not at all confident’; 10 = ‘very confident’). The score of all items is summed to yield the total score (range 0–130). A higher score represents higher self-efficacy in performing daily functional activities and self-management. The authors have back-translated [19] and validated the Chinese version of SSEQ in a convenience sample of 135 Chinese community-residing stroke survivors. The results showed high internal consistency (Cronbach’s alpha = 0.92). There were positive correlations between the total scores of the translated Chinese version of SSEQ, and General Self-Efficacy Scale (Spearman’s rho *r*_*s*_ = 0.48, *p* < 0.01) and Frenchay Activities Index (Spearman’s rho *r*_*s*_ = 0.51, *p* < 0.01), suggesting acceptable convergent validity.

##### Outcome expectation

An 11-item Chinese version of the Stroke Self-management Outcome Expectation Scale was developed based on Bandura’s construct of self-efficacy [16], and previous literatures on stroke self-management [4] and outcome expectation [20, 21] to measure participants’ current level of confidence that the desired outcomes will be resulted after performing the self-management behaviours. Each item is rated on an 11-point Likert scale (0 = ‘not confident at all’; 10 = ‘very confident’). The total score is summed (range 0–110). A higher score indicates higher confidence in likelihood of the outcomes to occur. An expert panel of two nurse academics, one nurse manager, three advanced practice nurses and two physicians performed assessment of content validity (Content validity index: 0.98). The scale was piloted in a convenience sample of 83 Chinese community-residing stroke survivors and showed high internal consistency (Cronbach’s alpha = 0.94).

#### Secondary outcomes

##### Stroke self-management behaviours

An 11-item Chinese version of the Stroke Self-management Behaviours Performance Scale was developed by the authors based on previous literatures about stroke recovery to measure participants’ satisfaction with their current performance in stroke self-management behaviours [4, 22, 23]. Each item is rated on an 11-point Likert scale (0 = ‘very dissatisfied’; 10 = ‘very satisfied). The total score is obtained by summing the scores of all items (range 0–110). A higher score indicates higher level of satisfaction with own performance in self-management behaviours. An expert panel of two nurse academics, one nurse manager, three advanced practice nurses and two physicians performed assessment of content validity (Content validity index: 0.98). The scale was piloted in a convenience sample of 83 Chinese community-residing stroke survivors and showed high internal consistency (Cronbach’s alpha = 0.93).

##### Health-related quality of life

The 49-item Stroke Specific Quality of Life Scale (SSQOL) will be used to measure participants’ health-related quality of life [24, 25]. It consists of 12 domains including self-care, vision, language, mobility, work/productivity, upper extremity function, critical-thinking, personality, mood, family roles, social roles, and energy. Each item is rated on a 5-point scale (0 = ‘couldn’t do it at all’ to 5 = ‘no trouble at all’; or 0 = ‘strongly agree’ to 5 = ‘strongly disagree’). The scores are summed to yield the total score (range 49–245) and domain scores. A higher total score indicates better health-related quality of life [24]. The authors have back-translated [19] and validated the Chinese version of SSQOL in a convenience sample of 135 Chinese community-residing stroke survivors. The results showed high internal consistency (Cronbach’s alpha of the total and domain scores: 0.63–0.93). The total score of the translated Chinese version of SSQOL was significantly correlated with the Chinese version of SSEQ (Spearman’s rho *r*_*s*_ = 0.68, *p* < 0.01) and Frenchay Activities Index (Spearman’s rho *r*_*s*_ = 0.60, *p* < 0.01), suggesting acceptable convergent validity. An additional 13 items will be used to measure participants’ changes in each domain and the overall health-related quality of life compared with their pre-stroke condition. Each item is rated on a 4-point scale from 1 ‘same as’ to 4 ‘a lot worse’.

### Depressive symptoms

The 15-item Chinese version of the Geriatric Depression Scale will be used to measure participants’ presence of depressive symptoms in the past week [26, 27]. Each item is rated on a yes/no format. A score will be given to the ‘yes’ items. The total score is calculated by summing each item score (range 0–15). A score of nine or above suggests moderate or severe depression. The scale has high internal consistency (Cronbach’s alpha = 0.78) and acceptable convergent validity. Significant correlation was found between the total scores of the scale and the London Handicap Scale (*r* = −0.30, *p* < 0.01) [28].

### Community reintegration

The 11-item Chinese version of the Reintegration to Normal Living Index will be used to measure participants’ level of community reintegration after stroke [29, 30]. Participants will be asked about the extent to which each statement with regards to six domains (mobility, self-care, activities, role within the family, comfort with relationships, and ability to handle life events) describes their current situation. All items are rated on a 4-point scale (1 = ‘does not describe my situation’ to 4 = ‘fully describes my situation’). Two subscale scores ‘daily functioning’ and ‘perception of self’, and a total score will be summed and normalised to 100 (range 25–100). A higher score indicates higher perceived community participation. The index has high internal consistency (Cronbach’s alpha = 0.92) and good convergent validity. Significant associations were reported between the Index and Frenchay Activities Index (*r* = 0.44, *p* < 0.001), and Personal Wellbeing Index (*r* = 0.25, *p* = 0.033) [30].

### Usefulness of the programme

Participants receiving the self-management programme will be assessed about their: 1) extent of overall programme participation by calculating the average of participants’ percentage of attendance at the programme; 2) self-reported frequency of viewing the videos on the DVDs; 3) number of personal goals attained upon programme completion; 4) reasons for not being able to attain the goals; and 5) qualitative comments about usefulness of the DVDs and areas for further improvement of the programme.

### Demographic and clinical information

Demographic data of the participants including age, gender, educational level, occupation, marital status, living condition, accommodation, main carer, social history, and financial assistance will be recorded. Clinical information including duration after stroke onset, type and location of stroke, past health history, current medication regimen, medical follow-up, smoking habits, use of alcohol, use of assistive devices and health services utilisation will be recorded. Furthermore, physical examination will be performed by the research assistant using instruments including MMSE, Glasgow Coma Scale, National Institutes of Health Stroke Scale (NIHSS), and the Barthel Activities of Daily Living (ADL) Index.

### Data collection procedures

All potential participants will be identified by reviewing their medical records or referrals by stroke nurses at the study venues. The principal investigator or research assistants will screen the participants in a face-to-face interview for their eligibility and willingness to participate in the study. Written informed consent will be obtained from those who are eligible. A card indicating participants’ involvement in the study and means of urgent contact will be provided to each participant after obtaining the consent. The consented participants’ demographic and clinical information will be retrieved from their medical records. Baseline and follow-up assessments will be conducted by two research assistants. The participants will be scheduled via phone by a research assistant for baseline assessment within one month after their discharge from hospital. Immediately after baseline assessment is completed, the participants will be randomly assigned to either the intervention or the control group. At 8 weeks after randomisation, the participants will be scheduled via phone by the research assistant again for follow-up assessment. The research assistants will administer the assessment tools in a face-to-face interview at the participants’ homes. The administration of the questionnaires has been pilot tested among six Chinese community-dwelling stroke survivors (mean age 55 years, SD 10.35, range 35–64 years). It took an average of one hour to complete the six questionnaires. Another research assistant will call the participants in the intervention and control groups at the time immediately after programme completion to collect their feedback on the programme (Table 3). The research assistants will be trained to administer the assessment tools consistently and non-judgmentally; and be reminded of the importance of confidentiality and safe storage of data. Inter-rater reliability between research assistants will be checked using Kappa statistics before data collection.

**Table 3 Tab3:** Summary of measurements and study outcomes

Measurements	Instruments	Group	Baseline	Follow-up	Outcomes	
					1°	2°
Self-efficacy	SSEQ	IG, UG	×	×	×	
Outcome expectation	SSOES	IG, UG	×	×	×	
Satisfaction with performance of SSMB	SSBPS	IG, UG	×	×		×
Health-related quality of life	SSQOL	IG, UG	×	×		×
Depressive symptoms	GDS	IG, UG	×	×		×
Community reintegration	RNLI	IG, UG	×	×		×

*GDS* Geriatric Depression Scale, *IG* Intervention group, *RNLI* Reintegration to Normal Living Index, *SSBPS* Stroke Self-management Behaviours Performance Scale, *SSEQ* Stroke Self-Efficacy Questionnaire, *SSMB* Stroke self-management behaviours, *SSOES* Stroke Self-management Outcome Expectation Scale, *SSQOL* Stroke Specific Quality of Life Scale, *UG* Usual care group

1°: Primary outcome

2°: Secondary outcome

### Non-participant observation

An expert panel member will conduct non-participant observation of the first session of the programme. The purpose is to identify the extent to which the programme was delivered according to the protocol using a Likert scale from 1 ‘A small extent’ to 5 ‘A large extent’, participants’ level of participation, and facilitators of and barriers to their participation.

### Statistical analysis

Statistical analyses will be performed using the IBM SPSS Statistics version 22 (SPSS Inc., Chicago, IL, USA). All primary analyses will be conducted on an intention-to-treat basis. No interim analyses will be undertaken. Descriptive statistics will be used to summarise participants’ baseline characteristics and outcome variables. All continuous outcomes will be assessed for normality in distribution. Appropriate transformation of skewed data will be performed before analysis. Chi-square tests and independent t-tests will be used to compare the demographic and clinical characteristics, and mean scores of outcomes between the intervention and control groups at baseline. A generalised estimating equation (GEE) model will be employed to assess differential change of the primary and secondary outcomes across the time points (baseline and eight weeks after randomisation) between the two groups. Adjustment will be made for potential confounding demographic and clinical variables, including gender, age, number of strokes, NIHSS, and the Barthel ADL Index, that were ‘unbalanced’ between the two groups (*p* < 0.25) [31, 32]. The longitudinal association of self-efficacy and outcome expectation with secondary outcomes will be examined using GEE model. GEE model can account for intra-correlated repeated measures data and accommodate missing data caused by dropouts, provided the data are missing at random [33], and is particularly suitable for intention-to-treat analysis without imputation for missing data. Significance level will be set at two-sided *p* < 0.05 and all statistical tests will be two-tailed.

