### Sample size estimation

Primary outcome of this trial is stroke survivors’ self-efficacy in performing self-management behaviours measured by the Stroke Self-Efficacy Questionnaire at eight weeks after randomisation. A sample size of 64 per group (128 for two groups) is required to detect a significant mean difference in self-efficacy between groups for a medium effect size of 0.5 [14] with significance set at 0.05 and a power of 0.8 [15]. Taking into consideration an attrition rate of 19 % over six months among stroke survivors [14], the final sample size is 160 (80 participants per group). Recruitment of participants is anticipated to take 12 months.

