### Randomisation

Eligible participants, immediately after providing baseline assessment data, will be randomly assigned in a 1:1 ratio to the intervention or the control group according to a computer-generated random schedule in permuted blocks of six with no stratification. A statistician who is not involved in recruitment, treatment allocation, and outcome assessment will generate the randomisation numbers. The statistician will put the randomly sequenced numbers indicating group assignment into sealed, opaque, containing a carbon paper inside, and sequentially numbered, otherwise identical, envelopes. Upon enrolling each participant, a research assistant who is not involved in recruitment and outcome assessment will take an envelope consecutively, write the participant’s study identifier on the envelope, open it and inform the principal investigator about the treatment allocation.

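### The trial is sized for a week-8 difference but tests change from baseline: 80% power then needs a correlation of about 0.5, and adjusting for baseline would be more precise

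*Protocol article*

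**What the plan says.** Protocol article, Sample size estimation: the primary outcome is named as "self-efficacy in performing self-management behaviours measured by the Stroke Self-Efficacy Questionnaire at eight weeks after randomisation". The planning assumptions are a standardised difference of 0.5 between the arms, a 5% significance level and 80% power. The result is stated thus: "A sample size of 64 per group (128 for two groups) is required". Allowing for 19% attrition, this becomes 80 per group, 160 in all. No correlation between baseline and follow-up scores enters the calculation, and none is given elsewhere in the article.

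Protocol article, Statistical analysis: a GEE model will "assess differential change of the primary and secondary outcomes across the time points (baseline and eight weeks after randomisation) between the two groups". Baseline is thus one of the two outcome time points. The named adjustment covariates are gender, age, number of strokes, NIHSS and the Barthel index, used when the arms differ at p < 0.25. The baseline score of the outcome is not named as a covariate. Tests are at the 5% level ("Significance level will be set at two-sided").

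Protocol article, Randomisation: immediately after the baseline assessment, participants "will be randomly assigned in a 1:1 ratio to the intervention or the control group". Table 3 shows all six scales measured in both arms at both visits.

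**The concern.** The sample size section and the analysis section describe different contrasts. The first compares week-8 means. The second compares the change from baseline to week 8, which in a two-visit GEE is the group-by-time term. The two have the same expectation under randomisation but not the same variance, and the ratio depends on a correlation that the article does not state.

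Two things are at stake. If SSEQ scores soon after discharge correlate weakly with scores at follow-up, the trial has less power than it states. And whatever the correlation, the change contrast subtracts an estimated baseline difference between arms that randomisation already sets to zero in expectation. That adds noise which baseline adjustment avoids, using scores that are collected anyway.

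**Working it through.** **Inputs.** From the article: d = 0.5, two-sided α = 0.05, 64 evaluable per group, 1:1 allocation, 19% attrition. Assumed because the article does not give them: the correlation ρ (range shown), equal SDs at both visits, and d expressed in units of the week-8 SD.

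**Step 1: reproduce the stated size.** A two-sample t-test with d = 0.5 needs 63.8, so 64 per group, and 64 per group gives power 0.801. Attrition: 64 / 0.81 = 79.01, rounded up to 80 per group, 160 in total. The stated figures reproduce as a plain comparison of week-8 scores.

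**Step 2: variance of each contrast**, relative to the week-8 comparison (factor 1).
- Differential change: with complete data at two visits, the group-by-time term equals the difference in mean change. Var(Y₈ − Y₀) = σ² + σ² − 2ρσ² = 2(1−ρ)σ², so the factor is 2(1−ρ). It is at most 1 only when ρ ≥ 0.5.
- Week-8 difference adjusted for baseline: the factor is 1−ρ², which is never above 1.
- Gap: 2(1−ρ) − (1−ρ²) = (1−ρ)², positive for every ρ < 1.
- Ratio of adjusted to change variance: (1−ρ²) / [2(1−ρ)] = (1+ρ)/2. At ρ = 0.5 this is 0.75, a 25% smaller variance; √0.75 = 0.866, a 13% smaller standard error.

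**Step 3: power at 64 per group**, from the noncentral t with effect 0.5/√(factor), and the evaluable number per group needed for 80%.

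| ρ | Power, change | Power, baseline-adjusted | n per group for 80%, change | n per group for 80%, adjusted |
|---|---|---|---|---|
| 0 | 51% | 80% | 127 | 64 |
| 0.2 | 60% | 82% | 102 | 62 |
| 0.3 | 66% | 84% | 89 | 59 |
| 0.4 | 73% | 87% | 77 | 54 |
| 0.5 | 80% | 90% | 64 | 49 |
| 0.6 | 88% | 94% | 52 | 42 |
| 0.7 | 95% | 98% | 39 | 34 |
| 0.8 | 99% | 99.7% | 27 | 24 |

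At ρ = 0.3, 80% power after 19% attrition would need 89 / 0.81 → 110 per group (220 in total) for the change contrast, and 59 / 0.81 → 73 per group (146 in total) for the adjusted one.

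**Step 4: check by simulation.** With 1,500 simulated trials per value of ρ and 64 per group, the GEE group-by-time test (exchangeable working correlation) rejected in 68%, 80% and 96% of trials at ρ = 0.3, 0.5 and 0.7. Analysis of covariance rejected in 84%, 89% and 97%. This agrees with the formulas.

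**Step 5: how far the 0.5 threshold moves.**
- Unequal SDs: the change contrast matches the week-8 comparison when ρ ≥ SD(baseline) / (2 × SD(week 8)). SD ratios of 0.8 to 1.2 give thresholds of 0.4 to 0.6.
- More than 64 followed up: with n per group analysed, the stated power needs 2(1−ρ)/n ≤ 1/64, so ρ ≥ 1 − n/128. This gives 0.44 for n = 72 and 0.375 for n = 80.
- 80 per group at baseline, 64 at follow-up, exchangeable GEE keeping everyone: the factor is (1−ρ²) + (1−ρ)² × 64/80. Setting it to 1 gives ρ² + 8ρ − 4 = 0, so ρ = 0.47. With an independence structure it stays at 0.5.

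**The case against.** The strongest reply is that no shortfall has been shown. The article gives no ρ, and the same scale administered by interview at home, eight weeks apart, could well correlate above 0.5. At ρ = 0.7 or 0.8 the change contrast has 95% or 99% power and the gap to baseline adjustment almost closes. The 19% attrition is quoted over six months, while follow-up is at eight weeks; if fewer drop out, the threshold falls towards 0.375. The effect of 0.5 comes from a cited source and could be standardised by the SD of change, in which case 80% holds at any ρ. The article does not print the model terms, so a baseline group effect is inferred. Analysis of covariance also drops participants without follow-up, whereas GEE was chosen partly to accommodate dropout.

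Much of this stands as a qualification of the power claim, which has to be read as conditional. The reading of d as a change-score effect fits poorly with a sample size section that defines the outcome at eight weeks. Differential change between arms over two visits is, on its ordinary reading, the group-by-time contrast; if a common-baseline model was intended, the text should say so. The dropout point holds against plain analysis of covariance but not against the common-baseline model. None of these points removes the loss of precision relative to baseline adjustment at every ρ below 1.

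**Conclusion.** The concern holds. The sample size calculation and the planned primary test do not match. Under the planning conditions (64 evaluable per group, equal SDs, d = 0.5 in week-8 SD units), the stated 80% is secured only if ρ is at least 0.5. Whether the trial is actually underpowered cannot be settled from the article.

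The second conclusion needs no particular value of ρ: the change contrast is valid but less precise than a baseline-adjusted comparison. Under the same conditions, the adjusted analysis meets the stated 80% at any correlation; at ρ = 0 it only equals the week-8 comparison, and it exceeds it otherwise. This is a matter of efficiency and internal consistency, not of bias. It should be corrected because the remedy needs no new data and no extra participants.

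**What to change.** State the primary contrast as the week-8 between-group difference in SSEQ adjusted for baseline SSEQ in all participants, whether or not the arms look unbalanced. Either of two forms will do:

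- analysis of covariance of the week-8 score on arm and baseline score; or
- the two-visit repeated-measures model with one common baseline mean, so that arm enters only at week 8. This keeps the GEE framework and the participants who lack follow-up. It needs a correlated working structure: under independence the arm effect reduces to the unadjusted week-8 difference and the gain is lost.

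Use the same form for outcome expectation and the secondary scales. In the sample size section, say that 64 per group was computed for the week-8 comparison without using the correlation, so that 80% is a lower bound under the adjusted model if the other planning assumptions hold.

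The cost is a change of wording. Baseline scores are already collected, the sample size stays at 160 and the same software can be used. The one trade-off is that plain analysis of covariance uses only participants with follow-up, which is a reason to prefer the common-baseline model if dropout is appreciable.

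### Choosing adjustment covariates by baseline tests at p < 0.25 lets chance, not prognosis, set the model; in the planned GEE the adjustment is probably inert, and the cost elsewhere is small and conservative

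*Protocol article*

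**What the plan says.** The Statistical analysis section of the protocol article first plans significance tests of baseline data: "Chi-square tests and independent t-tests will be used to compare the demographic and clinical characteristics, and mean scores of outcomes between the intervention and control" arms. The treatment effect comes from a two-visit model: "A generalised estimating equation (GEE) model will be employed to assess differential change of the primary and secondary outcomes across the time points". Adjustment is then made for "potential confounding demographic and clinical variables, including gender, age, number of strokes, NIHSS, and the Barthel ADL Index", but only for those meeting the condition in "NIHSS, and the Barthel ADL Index, that were ‘unbalanced’ between the two groups", with a threshold of p < 0.25. The list is introduced as examples, so it is not closed. The section does not say whether a selected covariate enters as a main effect, as an interaction with time, or in some other way.

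The Randomisation section says that participants, "immediately after providing baseline assessment data, will be randomly assigned in a 1:1 ratio", and describes a "computer-generated random schedule in permuted blocks of six with no stratification". Baseline variables are therefore fixed before allocation, and none of them constrains it.

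**The concern.** Baseline differences between properly randomised arms arise by chance. A test of such a difference says nothing about whether the variable predicts self-efficacy at week 8, and prediction is what makes a covariate worth having. A rule based on these tests will usually omit a strong predictor and will sometimes admit a useless one.

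Two things could follow, depending on how the covariates enter. If they cannot influence the group-by-time contrast, the stated adjustment is a formality. If they can, the reported standard error comes from a model chosen by chance imbalance and need not match the true spread of the estimator. Either way, precision available from variables the plan already names is given up.

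**Working it through.** **Plan's own figure.** Standardised difference 0.5, two-sided 0.05 and power 0.8 (Sample size estimation) need 63.77, so 64 per group, by the t-test; power at 64 is 0.801. For 19% attrition, 64 / (1 − 0.19) = 79.01, so 80 per group and 160 in all. The plan's figures are reproduced. The simulations below use 64 per group and a difference of 0.5.

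**Selection.** Under randomisation a baseline p-value is close to uniform, so P(p < 0.25) is about 0.25 for each covariate.
- Expected number selected: 5 × 0.25 = 1.25. This needs no independence.
- If the five are independent: none selected 0.75^5 = 0.237, at least one 0.763, all five 0.25^5 = 0.001. NIHSS and Barthel are plausibly correlated, so these three are indicative only.

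**Main effects in the group-by-time GEE.** Write the mean as b0 + b1·group + b2·time + b3·group·time + c·X, with X constant over time. With both visits observed, the estimate of b3 is the difference between arms in mean change, and c·X subtracts out of each person's change. In two simulated complete data sets, b3 and its SE were the same with and without all five covariates: 0.1774 (SE 0.1527) and 0.4366 (SE 0.1415), under independence and exchangeable working correlation. With 19% of follow-up missing, the estimate moved by 0.002 to 0.012. The SE moved little: for example 0.1446 to 0.1431 (exchangeable) and 0.1478 to 0.1424 (independence).

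**A form in which covariates act on the contrast.** The results depend on whether baseline score is in the model. Assumptions, none of them in the documents: five independent normal covariates, two with no prognostic weight, jointly explaining 20, 35 or 50% of week-8 variance; baseline/week-8 correlation 0.6 where baseline is used. There were 8,000 trials per cell.

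| Model | Variance explained | Power, p < 0.25 rule | Power, all five fixed | Type I error, rule |
|---|---|---|---|---|
| Week 8, no baseline score | 20% | 82% | 86% | 4.1% |
| | 35% | 85% | 93% | 3.1% |
| | 50% | 87% | 98% | 2.2% |
| Week 8 with baseline score | 20% | 93% | 94% | 4.5% |
| | 35% | 94% | 96% | 4.3% |
| | 50% | 95% | 97% | 4.2% |

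A repeat with baseline score gave type I error of about 4.1 to 4.4% and a loss of 1 to 3 points. Monte Carlo error near 5% is √(0.05 × 0.95 / 8,000) = 0.24 points, so the shortfall in the 20% row is only about twice the noise.

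**Why baseline score matters.** Take week-8 variance as 1 and equal covariate effects at both visits. Without baseline, the five covariates cut residual variance from 1 to 0.80, 0.65 or 0.50. Baseline score alone leaves 1 − 0.6² = 0.64. Adding the five gives (1 − R²) − (0.6 − R²)² / (1 − R²):
- R² = 0.20: 0.80 − 0.16/0.80 = 0.60
- R² = 0.35: 0.65 − 0.0625/0.65 = 0.55
- R² = 0.50: 0.50 − 0.01/0.50 = 0.48

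Much of what the covariates predict is already in the baseline score.

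**Direction.** In a separate run without baseline score (20,000 trials, five equally prognostic covariates), mean reported SE against true SE under the rule was 0.172 against 0.158 at R² = 0.3 and 0.167 against 0.144 at R² = 0.5. The reported SE is too large. Mean estimates stayed at 0 and 0.5, so there was no bias.

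**The case against.** The strongest reply is that the plain reading of the section is main effects, for which the choice of covariates barely touches the primary result, and that how they enter is a detail a separate analysis plan may settle. This stands against any flat claim that the primary interval will be too wide. It does not rescue the rule, which is then an adjustment in name only.

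Several stronger readings are tempting, and the documents do not support them:
- **That the rule inflates false positives or biases the effect.** Where it has any effect, type I error falls below 5% and the estimate is unbiased.
- **That power losses of 4 to 11 points and type I error down to 2.2% apply here.** Those figures belong to a week-8 model without baseline score. The planned GEE contains the baseline score as a response, and a sound replacement would include it as a covariate. For a change-score outcome with equal covariate effects at both visits, power was 87% under the rule and 87% with all five fixed.
- **That the trial falls short of its planned power.** Every simulated power under the rule was above 80%. What is lost is a gain forgone.
- **That the model can be steered by the outcome.** The screen uses variables collected before randomisation and a stated threshold. The open list leaves some freedom over candidates, but week-8 data play no part in the screen.

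**Conclusion.** The point holds in a limited form. The stated rule selects covariates by chance imbalance, with about a 25% chance for each. In the model as most naturally read, it then adjusts essentially nothing. If the covariates are entered so that they act on the week-8 contrast alongside baseline score, the harm is a slightly conservative test (about 4.1 to 4.5%) and about 1 to 3 points of power. Those sizes rest on an assumed correlation of 0.6 and on covariates explaining 20 to 50% of week-8 variance; neither is in the documents, and other values would move the figures. The selection probability and the cancellation with complete data do not rest on those assumptions. This is a cheap improvement to a poorly chosen rule and no threat to the trial's validity.

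**What to change.** Delete the p < 0.25 rule. For the primary comparison, model the week-8 score on group, baseline score and the five covariates the plan already names (age, gender, number of strokes, NIHSS, Barthel), fixed in advance and kept whatever the observed balance. State how they enter, so that they act on the week-8 contrast. Time-constant main effects in the two-visit group-by-time GEE would not do this. Covariate-by-time terms would, but they amount to a regression of change and gain nothing when covariate effects are equal at both visits, so the baseline-adjusted week-8 model is preferable. Present baseline characteristics descriptively, without tests; once the rule is gone, that last change is largely one of presentation.

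The cost is wording and about five degrees of freedom out of 128 analysed participants. No new data are needed and the sample size of 160 is unaffected.
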